#### Intake assessment

After consenting/assenting, participants also sign a release of medical records permitting the release of information on their SRH, PrEP screening and monitoring results, and other referrals and care pertinent to the study.

Participants take a breathalyzer test to detect recent alcohol use (conducted earlier in the appointment because of the limited detection window for alcohol breath scans) and provide urine for drug screening, locator information is collected, and a photograph of the participant is taken to identify the participant for subsequent appointments. This photo is returned or shredded at the final appointment. The participant then completes a baseline questionnaire on a computer tablet via audio computer-assisted self-interview (ACASI) in either English or Setswana (see AGYW Health CoOp Questionnaire in Supplementary File 3). Trained field staff are available to assist the participant at any time and provide referrals based on prompts related to self-reported violence, symptoms of psychological distress, or suicidal ideation experienced in the past 3 months that are triggered as the participant completes the questionnaire. The questionnaire is derived from components of the youth-specific modification of the Revised Risk Behavior Assessment (RRBA) [54], which has been adapted and modified for many studies in South Africa. The modified RRBA for this study contains sections on PrEP knowledge, contraception and other SRH services access and utilization, sexual communication, STI symptoms, alcohol and other drug use, relationship equity and sexual control, economic dependence, personal agency, psychological distress, victimization, and peers and social support. After completing the questionnaire, urine drug screening results are provided to assess the recent use of amphetamine, methamphetamine, benzodiazepine, cocaine, marijuana, opioids, and MDMA. These screening tests are repeated at 3-, 6-, and 9-month follow-up assessments.

After the intake appointment, participants interested in initiating PrEP are referred to the youth-friendly nurse in their respective study clinic or the study’s roaming nurse to screen for PrEP eligibility using the National Department of Health (NDoH) guidelines. Baseline screening for PrEP involves reporting of no MDR-TB (part of the study eligibility criteria), HIV and pregnancy testing (conducted prior to the intake process to confirm HIV-negative and not pregnant), estimation of creatinine clearance, and hepatitis B virus (HBV) screening. Contraindications for PrEP use includes poor renal function (estimated creatinine clearance < 60 mL/min) and absence of the hepatitis B surface antigen and antibody. Presence of HBV is not a contraindication for PrEP; however, liver function monitoring is advised if PrEP is initiated. Participants not eligible for PrEP are linked to the public health clinic to receive the standard of care for each respective medical condition. Individuals who are not eligible for PrEP can still remain enrolled in the study.

Participants may decide to initiate PrEP at any time during the study. However, those who do not initiate PrEP during their baseline appointment have to repeat all PrEP eligibility screening. Participants who decide to initiate PrEP are counselled on the importance of adherence and using other protective strategies for up to 20 days of daily dosing before protective levels in vaginal tissue are achieved. Participants are also given guidance on proper management of mild side effects that may occur after initiation and are advised to continue to use condoms and birth control to protect themselves against other STIs and unplanned pregnancy, as PrEP does not provide this type of protection.

Clinic visits to test for HIV and pregnancy status are scheduled 1 month after initiation of PrEP and every 3 months thereafter. At 6 months post initiation of PrEP, screening of creatinine levels is conducted to estimate creatine clearance. If a participant tests positive for HIV at any point in the follow-up appointments, PrEP is stopped for that participant and an active referral is provided for test and treat according the South African HIV guidelines. Nonclinical behavioral study data collection follow-up visits continue to occur at 3, 6, and 9 months post enrollment regardless of whether or when PrEP is initiated or when a participant’s PrEP clinic visits take place.

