### Data collection: adolescent girls and young women level

#### Recruitment

AGYW are recruited in communities that are in the study clinic’s catchment area. Recruitment is conducted through research study staff, who may also be assisted by trained WBOTs associated with the study clinics. However, screening is only conducted and performed by research study staff. Recruitment is conducted via street outreach at identified areas where AGYW are known to frequent. Street outreach is an established recruitment method that has been used successfully in previous research studies [50–53], including Tshwane WHC studies to reach and recruit a high number of women most at risk of HIV. Study staff visit these hotspots regularly to establish a known presence in the community and gain rapport with community members. Recruitment also is conducted through referrals from the clinic or other staff who conduct HIV and/or pregnancy testing in the community, such as HIV and AIDS, STI, and TB (HAST) counselors.

Participant eligibility criteria include the following: (1) identify as female; (2) HIV negative status; (3) between ages 16 and 24 years; (4) have had condomless sex in the past 3 months with a male partner; (5) not currently pregnant and do not want to get pregnant within the next year; (6) interested in taking a daily pill to prevent HIV (PrEP); (7) not having previously participated in the formative phase of the study; (8) not previously or not currently participating in any other PrEP-related project or research study; (9) not previously or not currently participating in any other HIV study in Tshwane; (10) not on multidrug-resistant tuberculosis (MDR-TB) treatment; (11) lives in one of the target communities; (12) intends to stay in the Tshwane district for the next 12 months; (13) agrees to provide contact information; (14) willing to undergo rapid HIV testing; and (15) willing to undergo pregnancy testing.

Because of the eligibility requirement of an HIV-negative and nonpregnant status, interested potential participants must first consent to rapid testing for HIV and pregnancy to confirm eligibility. Additionally, co-enrollment in another HIV study is also checked and any individual who is currently enrolled is excluded.

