#### PrEP navigation after PrEP initiation

Although the South African National Strategic Plan for HIV, TB and STIs (2017–2022) [47] outlines the availability of PrEP for all AGYW who are HIV-negative and at risk of HIV, PrEP roll-out in public health clinics has yet to occur. Consequently, a majority of public health clinic staff have not been trained on PrEP prescribing and dispensing protocols. Prior to the national roll-out, the PrEPARE Project partnered with the NDoH to train youth-friendly nurses and pharmacists charged with supporting and implementing PrEP delivery from all study clinics on standardized PrEP protocols. A roaming nurse has been hired to assist in the management and support of dispensing PrEP where there is a shortage of trained clinic staff.

PrEP navigation, which occurs through phone calls and text messaging, provides participants in the YWHC intervention arms who are on PrEP with much-needed support, specifically in the first 1 to 2 weeks of PrEP initiation where many participants may experience minor side effects that often lead to PrEP discontinuation. Study staff work with participants to develop feasible plans that can support the daily use of PrEP, such as the pill boxes they receive, adherence strategies, social support, and addressing other concerns about PrEP. Participants also are reminded about their upcoming refill and check-up appointments. This navigation occurs throughout the study duration as participants are due for their refills.

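### The PrEP screening text prints absence of both hepatitis B markers as a contraindication, which as worded bars women with neither marker while allowing women who have HBV

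*Protocol article*

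**What the plan says.** All the relevant wording is in the Intake assessment section of the protocol article, in the text on screening for PrEP after enrolment.

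- Women who want PrEP go to a nurse, who is to "screen for PrEP eligibility using the National Department of Health (NDoH) guidelines".
- Two contraindications are then listed. One is an estimated creatinine clearance below 60 mL/min. The other is "absence of the hepatitis B surface antigen and antibody".
- The following sentence reads: "Presence of HBV is not a contraindication for PrEP; however, liver function monitoring is advised if PrEP is initiated".
- Women who are not eligible for PrEP are "linked to the public health clinic to receive the standard of care for each respective medical condition".
- They are not withdrawn: "Individuals who are not eligible for PrEP can still remain enrolled in the study".
- PrEP may be started later in the study, but "those who do not initiate PrEP during their baseline appointment have to repeat all PrEP eligibility screening".

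The Recruitment section lists 15 enrolment criteria. Interest in taking daily PrEP is one of them; HBV status is not.

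**The concern.** A list of contraindications tells the nurse whom to refuse. The second item, as printed, tells her to refuse women who show neither the surface antigen nor the antibody. The sentence after it tells her that HBV itself is no reason to refuse. The text therefore admits women with the virus and turns away women with no marker of it, without explanation.

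Two things would be at stake if the sentence were followed. The first is participant protection. Enrolment requires a negative HIV test, condomless sex in the past 3 months and interest in PrEP, so anyone refused on this ground is an at-risk woman who said she was interested in the trial's prevention drug. The second is measurement. PrEP uptake and adherence are primary outcomes (Outcomes section). A refused woman stays enrolled and, unless she starts later, counts as not having taken up PrEP.

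**Working it through.** No figure in the plan bears on this rule, so the check is mainly a reading of the sentences against each other.

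**Step 1: what the list means.** The noun is plural and two items follow it. Reading *and* as a joint condition (poor renal function together with absent markers) would leave one contraindication, not several, and is not credible. The second item therefore stands as a bar on its own.

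**Step 2: apply the two HBV sentences to each marker pattern.** This takes presence of HBV to mean that the surface antigen is present.

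| Surface antigen | Antibody | Result as printed |
|---|---|---|
| present | absent | may start, liver monitoring advised |
| present | present | may start, liver monitoring advised |
| absent | present | not caught by the printed bar |
| absent | absent | contraindicated |

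The only pattern refused is the one with no HBV marker at all.

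**Step 3: look for a correction or a reason.** The Intake assessment, Recruitment, PrEP navigation and Follow-up assessments sections contain no statement that women with neither marker may start PrEP, no separate provision for them, and no rationale for refusing them.

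**Step 4: follow a refused woman through the trial, if the printed rule were applied.**

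1. HBV status is not an enrolment criterion, so she is already enrolled when the rule meets her.
2. She remains in the study.
3. Under Analysis, AGYW level, Aim 3 is analysed by intention to treat and uptake means any PrEP use. Unless she starts later, she is a non-user in the denominator. A start after month 3 but within the 9 months costs only the 3-month uptake measure.
4. Under Follow-up assessments, dried blood spots are taken only from women who report being on PrEP, so while off PrEP she gives no drug-level data.
5. The Study design section gives PrEP and SRH provision in all four conditions, and the screening text makes no distinction between them. The rule is the same throughout.

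**Step 5: scale.** The article has 12 clinics with 75 women each: 12 × 75 = 900. Each condition has 3 clinics (3 × 75 = 225) and each level of a factor has 6 (6 × 75 = 450). One woman who would have started and never does changes any-use uptake by 1/225 = 0.44 percentage points in her condition and 1/450 = 0.22 in each factor level, before attrition. These are reciprocals of the sample sizes and hold for any non-starter, whatever the reason. They do not measure the effect of this rule, because the number refused is not in the document.

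**The case against.** The best defence has three parts.

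First, the two HBV sentences do not contradict each other in logic. A rule that admits antigen-positive and antibody-positive women and refuses only those with neither is odd but possible, and a condensed article need not explain it; it gives no reason for the creatinine threshold either. This stands as far as it goes: a reader might infer a formal contradiction, and there is none. What remains is an unexplained bar on the one group with no HBV marker, beside a sentence saying that HBV is not a bar.

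Second, the working rule lies elsewhere. Nurses screen by the NDoH guideline, and the project trained the nurses and pharmacists charged with "implementing PrEP delivery from all study clinics on standardized PrEP protocols". If they followed these, nobody was refused. This also stands, and it limits the consequence. It does not make the printed sentence right, and the article is what readers will use to learn who could receive PrEP.

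Third, two further inferences are tempting and go beyond the text. One is that women with neither marker have no condition for which they could be linked to care. The article does not define the conditions it means, and susceptibility to HBV might be acted on. The other is that repeat screening would refuse the same woman for good. The criterion would be applied again, but marker status can change, so a lasting bar is not established.

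**Conclusion.** The rule is wrong as written. Taken literally, it withholds PrEP from enrolled women who are interested in it and have neither HBV marker, while women with HBV may start, and the article offers neither a reason nor a correction. The likeliest explanation is a drafting error. Because the NDoH guideline is not shown, the intended rule cannot be confirmed.

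The conclusion rests on the plain reading of the list and on the absence of any correcting text. It does not rest on a claim about field practice. A reader might infer that women were in fact refused; the document does not show this, and the number may be zero. A reader might also infer a bias between conditions, but the same rule applies in all four. A loss of power or a ceiling on uptake cannot be claimed either, since either would need the share of women barred and the article gives none.

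The sentence should be corrected, because it governs access to the study drug and the correction is cheap. Confidence is medium, since the intended wording is not available.

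**What to change.** 1. Rewrite the sentence so that it gives the HBV rule as it stands in the NDoH guideline used. Remove absence of both markers from the contraindications unless that guideline contains it.
2. State what is done for women with neither marker.
3. Check the PrEP screening form against the corrected sentence.
4. Only if the form carries the printed rule, review the screening logs for refusals on that ground and re-offer PrEP screening to the women concerned.

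The certain cost is one or two sentences and one form check. Step 4 costs nothing unless the form is wrong. If it is, the trial is still recruiting and the plan already allows PrEP to be started during follow-up after repeat screening, so no new procedure is needed.

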#### Sexual and reproductive health services

All participants who complete their baseline appointment are actively referred to the designated youth-friendly nurse or youth-friendly service at their respective study clinic for SRH services; specifically, birth control services. Follow-up on these linkages is conducted at the 3-month follow-up appointment for participants in the control groups and during monthly check-ins for participants in the YWHC groups.

#### YWHC workshops

The YWHC workshops comprise a 2-session, 4-module program designed to build on the nexus of substance use, HIV, and GBV by increasing knowledge, skills, and agency to reduce GBV and substance use, and ways to decrease sexual risk and HIV incidence. Previous research in South Africa has shown positive outcomes with the WHC, including that women in the WHC were more likely to use condoms with their boyfriends during their last episode of sexual intercourse, more likely to use female condoms with their boyfriends in the past month, more likely to negotiate condom use, and less likely to report daily substance use at follow-up than women who were not in the WHC [38, 39, 52]. The workshops also include voices and quotes from the formative focus group discussion participants (see Table 2 for an overview of the workshops). Typically, workshops are conducted approximately 7 to 10 days apart, but can be completed on the same day and in either order because of limited availability of the participants; for example, some participants are full-time students. Both workshops end with participants developing an individualized and personalized risk-reduction action plan with assistance from staff. Also, any relevant referrals are offered. Participants also receive toiletry kits and pill boxes with a colorful bag to discreetly store their PrEP. Once both workshops are completed, participants complete a Satisfaction Form to provide feedback and suggestions regarding the intervention. Staff conduct further follow-up with participants individually to check in on their personal action plans at least monthly via mobile phone or in person.

**Table 2 Tab2:** Overview of the YWHC Workshops

**Workshop 1**	
**Topics**	
• Becoming an adult woman and influences	
• Sex, sexual expectations, and risk	
• Our reproductive bodies (female and male anatomy)	
• STIs and HIV	
• Ways to reduce risk	
• Male and female condoms	
• Ways of communicating, negotiating, and problem-solving	
• PrEP	
• Birth control	
• Action plan (complete Workshop 1 goals and steps in workshop booklet)	
**Workshop 2**	
**Topics**	
• Inequality and gender power	
• Becoming strong women and concern for how boyfriends treat you	
• Abuse and violence	
• Safety tips for going out	
• Alcohol and drug use	
• Parenting	
• The importance of education and goals	
• Social support, especially taking PrEP	
• Action plan (complete Workshop 2 goals and steps in workshop booklet)	

#### PrEP navigation after PrEP initiation

Although the South African National Strategic Plan for HIV, TB and STIs (2017–2022) [47] outlines the availability of PrEP for all AGYW who are HIV-negative and at risk of HIV, PrEP roll-out in public health clinics has yet to occur. Consequently, a majority of public health clinic staff have not been trained on PrEP prescribing and dispensing protocols. Prior to the national roll-out, the PrEPARE Project partnered with the NDoH to train youth-friendly nurses and pharmacists charged with supporting and implementing PrEP delivery from all study clinics on standardized PrEP protocols. A roaming nurse has been hired to assist in the management and support of dispensing PrEP where there is a shortage of trained clinic staff.

PrEP navigation, which occurs through phone calls and text messaging, provides participants in the YWHC intervention arms who are on PrEP with much-needed support, specifically in the first 1 to 2 weeks of PrEP initiation where many participants may experience minor side effects that often lead to PrEP discontinuation. Study staff work with participants to develop feasible plans that can support the daily use of PrEP, such as the pill boxes they receive, adherence strategies, social support, and addressing other concerns about PrEP. Participants also are reminded about their upcoming refill and check-up appointments. This navigation occurs throughout the study duration as participants are due for their refills.

#### Follow-up assessments

Participants in both study arms return for their 3-, 6- and 9-month behavioral and biological follow-up assessments. Research staff track participants using locator information provided during the intake appointment to help retain participants. The follow-up visit includes reconsenting; updating locator information; a follow-up questionnaire via ACASI; and biological testing for HIV, pregnancy, alcohol use (breathalyzer), and other recent drug use. Dried blood spots (DBS) also are collected at these appointments from participants who report to be on PrEP. The PrEP medication used for this study is a combination of FTC 200 mg/TDF 300 mg tablets. The DBS are used to assess the presence of tenofovir diphosphate (TFV-DP), a measure of cumulative and recent adherence, using a previously validated methodology [55].

#### Data management and quality assurance

To protect confidentiality, the study assigns each participant a unique alphanumeric study participant identification number (PID). This PID is the only link between the behavioral and biological data and the identifying information collected for locating participants for their follow-up interviews. Locator forms, consent/assent agreements, and any data that can be linked through the PID are stored separately from other data in double-locked file cabinets in locked rooms at the study’s project site, with restricted access.

Data collection for this study is conducted by highly trained staff from the community who develop a rapport with the study participants to engender trust and elicit the most accurate data possible. All staff sign a confidentiality agreement and are trained on the study’s Quality Assurance Protocol and Quality Management Plan (QMP). Study data are encrypted before they are transmitted daily from the field site to secure servers in the United States. The US-based data manager reviews additional automated quality control checks that the software generates each day. If any critical inconsistencies are noted, the data manager contacts the project director and the field supervisor to resolve these inconsistencies. The Principal Investigator, other members of the research team, and the field staff receive daily field activity reports.

#### Data and safety monitoring plan and data and safety monitoring board

Procedures have been put in place to address adverse events (AEs) or serious adverse events (SAEs), such as improper disclosure of information or mental or emotional discomfort. As specified in our Data and Safety Monitoring Plan (DSMP), SAEs are reported to the Principal Investigator and the South African Co-Investigator/Medical Director within 24 h of an occurrence and to the Data and Safety Monitoring Board (DSMB), the funding agency, and the Institutional Review Board within 72 h, with appropriate action taken immediately. The study does not interfere with any activities or reports that are part of the public health clinics’ standard operating procedures that do not directly affect the study participants adversely. The DSMP ensures that procedures have been set in place to safeguard the security, validity, and integrity of study data, and that study staff are trained on the policies and procedures for data management according to the Quality Assurance Protocol and QMP. The DSMP also outlines the data analysis plan including preliminary analyses of data for quality assurance and to track the progress of the study.

The study established a DSMB comprising three members: a psychologist, an infectious disease clinician, and a bioethicist. The DSMB will meet every 6 months during the trial to review study progress and ensure adherence to the DSMP. This board is independent from the researchers and the study sponsoring institution. Board members discussed whether stopping rules were necessary for this study; they determined that stopping rules were not necessary.

